### Intervention description {11a}

The probiotics (intervention) or placebo (control) will be mixed with breastmilk and administered by gastric tube when infants tolerate at least 3 mL breastmilk per meal. The breastmilk may however be administered as a bolus or continuous feeds. For the intervention group, the standard dose of 0.5 g will be mixed with 3 mL breastmilk. For the control group, 0.5 g of placebo containing only maltodextrin powder will be used. If the mother’s breastmilk is available, this will be primarily used; otherwise, donated breastmilk will be given. There will be no visible difference between the breastmilk containing probiotic supplementation and placebo. The dose will be administered as the first meal of the day once daily until the infant reaches 34 weeks of gestation. The dosage and method of administration will not change with increasing age and weight. If the infant does not tolerate the enteral feeds after the start of probiotic supplementation and the administrated volume drops below 3 mL, the supplementation will be paused and started again when the infant tolerates 3 mL per meal again. If the infant does not receive the planned dose, this must be noted in the case report form (CRF). Unopened probiotic supplements and placebo will be stored at room temperature in a nutrition kitchen.

### Criteria for discontinuing or modifying the allocated interventions {11b}

The supplementation of probiotics (intervention) or placebo (control) will be administered in the same manner as given in the ProPrems trial [12] and according to existing clinical routines previously mentioned for infants born after gestational week 28 in Swedish hospitals. Variation in the timing of the administration of the intervention is acceptable if local clinical routines for probiotic supplementation are already set. As the probiotic mixture has been reported to remain stable for 4 h, the intervention must be given within 4 h [70]. Otherwise, a new mixture must be prepared.

All researchers, medical, and nursing staff will be blinded until the final analysis has been performed. However, code breaking will occur in connection to a suspected unexpected serious adverse reaction (SUSAR) due to the seriousness of the situation.

### Strategies to improve adherence to interventions {11c}

All infants will be recruited as inpatients and the intervention will be completed before discharge. Thus, the compliance to intervention does not rely on legal guardians’ adherence to instructions, rather to research and health care personnel at the clinic.

### Relevant concomitant care permitted or prohibited during the trial {11d}

Infants participating in another intervention trial where main outcome includes incidence of NEC cannot be included in this trial, as stipulated in the exclusion criteria. Patient insurance applies to infants in the study, as with all other care during hospital admission, and all study participants will be treated according to the existing standard of care beyond the studied intervention.

### Provisions for post-trial care {30}

There is no anticipated need for post-trial care. Patients will receive adequate care during and after hospital admission irrespective of their allocation to the intervention or control group. All extremely preterm infants are followed up at a neonatal ward until 5 years of age in both Sweden and Denmark as per clinical routine.

### Outcomes {12}

Table 1 (complete cohort) and 2 (sub-cohort) include descriptions of primary, secondary, and other outcomes including analysis metric, method of aggregation and time points for outcome collection in the PEPS trial. Details of NEC and LOS will be collected for validation of diagnoses and understanding of disease events. Serious adverse events (SAE) will be collected for interim analysis. All covariates collected in the trial are relevant for analyzing the risk of developing the primary and secondary outcomes and will primarily be used for sensitivity analysis.

**Table 1 Tab1:** Description of outcomes with analysis metric, aggregation method, and time points in main cohort

Outcome variables complete cohort			
*Primary outcome variables*	*Analysis metrics*	*Method of aggregation*	*Time point*
Necrotizing enterocolitis	Incidence rate	Mean/Median	During study intervention (until 34 weeks of gestational age)
Necrotizing enterocolitis Bell Stage >II^a^ Verified	Incidence rate	Mean/Median	During study intervention (until 34 weeks of gestational age)
Necrotizing enterocolitis Bell Stage >III^a^ Verified	Incidence rate	Mean/Median	During study intervention (until 34 weeks of gestational age)
Necrotizing enterocolitis Operation	Date, time	Mean/Median	During study intervention (until 34 weeks of gestational age)
Abdominal symptoms	Incidence of free gas, intermural intestinal gas, inflated abdomen discolored abdomen, stagnant intestinal loop >24 h	Sum	During study intervention (until 34 weeks of gestational age)
Differential gastrointestinal diagnoses	Spontaneous intestinal perforation, Malrotation/volvulus, other	Sum	During study intervention (until 34 weeks of gestational age)
X-ray of the abdomen	Incidence rate	Mean/Median	During study intervention (until 34 weeks of gestational age)
Death	Incidence rate	Mean/Median	Third day postpartum until 40 weeks of gestational age
***Secondary outcome variables***			
Late-onset sepsis	Incidence rate	Mean/Median	During study intervention (until 34 weeks of gestational age)
Verified late-onset sepsis^b^	Incidence rate	Mean/Median	During study intervention (until 34 weeks of gestational age)
Late-onset sepsis Culture-proven	Type of pathogen	Sum	During study intervention (until 34 weeks of gestational age)
Late-onset sepsis date	Date of onset	Sum	During study intervention (until 34 weeks of gestational age)
Late-onset sepsis Peripheral line at onset	Yes/No	Mean/Median	During study intervention (until 34 weeks of gestational age)
Late-onset sepsis Central line at onset	Yes/No	Mean/Median	During study intervention (until 34 weeks of gestational age)
Use of antibiotics	Rate of prescription (number) Duration of treatment (days)	Mean/Median	During study intervention and until 40 weeks of gestational age
Length of stay	Number of days	Mean/Median	Length of stay at the neonatal intensive care unit Length of stay at homecare
Effect on microbiome	Fecal samples		1. Directly after inclusion ± 2 days 2. 14 ± 2 days gestational age 3. 34 weeks ± 2 days gestational age 4. 12 months corrected age ± 2 weeks
***Serious adverse event*** (Necrotizing enterocolitis, death and late-onset sepsis included)			
Bronchopulmonary dysplasia	Yes/No	Mean/Median	During study intervention (until 34 weeks of gestational age)
Respiratory distress syndrome	Yes/No	Mean/Median	From birth and during study intervention (until 34 weeks of gestational age)
Patent ductus arteriosus (PDA)	Yes/No	Mean/Median	From birth and during study intervention (until 34 weeks of gestational age)
Pulmonary hypertension	Yes/No	Mean/Median	During study intervention (until 34 weeks of gestational age)
Intraventricular hemorrhage	Yes/No	Mean/Median	During study intervention (until 34 weeks of gestational age)
Hydrocephalus	Yes/No	Mean/Median	During study intervention (until 34 weeks of gestational age)
Retinopathy of prematurity	Yes/No	Mean/Median	During study intervention (until 34 weeks of gestational age)

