***Characteristics/covariates***			
Pregnancies	Number	Mean/Median	Baseline
Preeclampsia	Yes/No	Mean/Median	Baseline
Chorioamnionitis	Yes/No	Mean/Median	Baseline
Infection pregnancy	Number of infections	Sum	Baseline
Antibiotics during pregnancy	Period	Sum	Baseline
Mode of delivery	Vaginal or Cesarean-section	Mean/Median	Baseline
Apgar-score	At 1, 5 and 10 minutes	Mean/Median, Sum	Baseline
Gender (x/y)	Boy/girl	Mean/Median	Baseline
Multiple birth	Yes/No	Mean/Median	Baseline
Gestational age	Number (gestation week)	Mean/Median	Baseline
Birth weight	Kilograms	Mean/Median	Baseline
Birth length	Centimeters	Mean/Median	Baseline
Birth head circumference	Centimeters	Mean/Median	Baseline
Z-scores from growth chart at birth	Reference Niklasson [73] and Fenton [74]	Standard deviation	Baseline
Respiratory support Intubation	Period of treatment	Mean/Median	From birth until 40 weeks of gestational age
Respiratory support Continuous positive airway pressure (CPAP)	Period of treatment	Mean/Median	From birth until 40 weeks of gestational age
Respiratory support High-flow nasal cannula	Period of treatment	Mean/Median	From birth until 40 weeks of gestational age
Respiratory support Low-flow nasal cannula	Period of treatment	Mean/Median	From birth until 40 weeks of gestational age
Patent ductus arteriosus closure strategies Paracetamol	Period of treatment	Mean/Median	From birth until 40 weeks of gestational age
Patent ductus arteriosus closure strategies Operation	Date	Mean/Median, Sum	From birth until 40 weeks of gestational age

^a^See definition of Bell Stage >II-III under “Plans for assessment and collection of outcomes {18a}”

^b^See definition of verified late-onset sepsis under “Plans for assessment and collection of outcomes {18a}”

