#### Reporting serious adverse events

All SAEs will be recorded in the eCRF and do not need to be documented immediately. However, to be able to carry out interim analyses, all SAEs must be documented no later than 2 weeks after the intervention has ended for each patient.

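### Table 1 stops counting bronchopulmonary dysplasia, retinopathy, pulmonary hypertension and hydrocephalus at 34 weeks, when dosing ends, although it follows other items to 40 weeks

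*Protocol article*

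**What the plan says.** All of this is in the protocol article.

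- **Four harms, to 34 weeks.** Outcomes {12}, Table 1, serious adverse event block: "Bronchopulmonary dysplasia Yes/No Mean/Median During study intervention (until 34 weeks of gestational age") and "Retinopathy of prematurity Yes/No Mean/Median During study intervention (until 34 weeks of gestational age"). Pulmonary hypertension and hydrocephalus have the same time point, "During study intervention (until 34 weeks of gestational age").
- **End of dosing.** Intervention description {11a}: "The dose will be administered as the first meal of the day once daily until the infant reaches 34 weeks of gestation".
- **Other items, to 40 weeks.** Table 1 follows death "Third day postpartum until 40 weeks of gestational age" and antibiotic use "During study intervention and until 40 weeks of gestational age". Four modes of respiratory support, and paracetamol or operation for PDA closure, are recorded "From birth until 40 weeks of gestational age".
- **Data entry.** Reporting serious adverse events: "all SAEs must be documented no later than 2 weeks after the intervention has ended". The stated reason is the interim analyses.
- **Role and source.** The section on serious adverse events lists all four among the expected events. The section on the data monitoring committee {21a} has that committee review all serious adverse events. Plans for assessment and collection of outcomes {18a} takes outcomes mainly from the Swedish and Danish neonatal registries (SNQ and DNQD).

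**The concern.** For these four items the window closes when dosing ends, so no diagnosis made after the end of dosing counts, although data on the same infants are collected for 6 more weeks. The split also separates related items. Intubation, CPAP and nasal cannula support run to 40 weeks, while the chronic lung diagnosis they bear on stops at 34. The article gives no reason for this.

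This is a rule the article states, not a detail left to another document. If the registries hold later diagnoses, the table as written tells the analyst to leave them out. If the team means to count them, the table is wrong. At stake is how complete the harm comparison will be for four recognised morbidities, in a trial meant to inform guidelines for this population.

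**Working it through.** The plan gives no figure to reproduce here. The check compares time points and does date arithmetic.

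**Inputs.** Gestational age at birth is 22+0 to 27+6 weeks (Study setting {9}), that is 22 × 7 = 154 to 27 × 7 + 6 = 195 days. The four windows and dosing end at 34 weeks. The longer rows of Table 1 end at 40 weeks. Serious adverse events are entered within 2 weeks of the end of the intervention.

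**Formula.** Postnatal age in days at week w = 7 × w − gestational days at birth.

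| Time | Born 22+0 | Born 27+6 |
|---|---|---|
| 34 weeks | 238 − 154 = 84 | 238 − 195 = 43 |
| 36 weeks | 252 − 154 = 98 | 252 − 195 = 57 |
| 40 weeks | 280 − 154 = 126 | 280 − 195 = 85 |

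**Share of the birth-to-40-week period covered.** 84/126 = 67% for the most immature infants and 43/85 = 51% for the most mature. In both cases 40 − 34 = 6 weeks (42 days) are left out.

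**Range for BPD.** The article gives no assessment age, so two are assumed to show the range.

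- *Status at 28 days of age.* The youngest infant at 34 weeks is 43 days old, and 43 > 28. Every infant reaches the assessment age inside the window, so nothing is lost.
- *Status at 36 weeks.* This falls 2 weeks after the window closes for every infant, so every case is lost.

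**ROP, pulmonary hypertension and hydrocephalus.** The documents do not say when these are diagnosed, so no share can be given.

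**Does the entry deadline widen the window?** For an infant dosed to 34 weeks the deadline is 34 + 2 = 36 weeks. It governs when an event must be entered, not which events count. It does not change the Table 1 time point.

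**The case against.** The case for leaving the table as it is has real parts.

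- **An on-treatment window is a recognisable choice.** Outcomes {12} says serious adverse events are collected for interim analysis, and none of the four is a named primary, secondary or tertiary outcome. This lowers the severity. It does not remove the point, because Objectives {7} says that effects on other common neonatal morbidities will be studied.
- **Later information may exist anyway.** Respiratory support to 40 weeks might let a later BPD status be derived, the registries may hold later diagnoses, and the data monitoring committee's remit carries no 34-week limit. All true, but Table 1 plans no such use, and the article names no comparable 40-week data for ROP.
- **A longer window delays the interim looks.** Moving the entry deadline past 40 weeks would put complete data back by at least 40 − 36 = 4 weeks per infant. This stands against moving the deadline, but not against adding a later final update.

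A reader might also infer more than the documents support:

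- *That BPD and ROP will be largely missed.* This needs the ages at diagnosis, which the article does not give.
- *That the outcomes are undefined.* The article condenses a fuller protocol, and its Additional file 1 is not shown. A missing definition is not a finding.
- *That no post-dosing harm is counted.* Death belongs to the serious adverse event block and runs to 40 weeks.
- *That the unequal window, about 6 to 12 weeks by gestational age at birth, is a flaw.* The spread is 84 − 43 = 41 days at 34 weeks and 126 − 85 = 41 days at 40 weeks, so a longer window leaves it unchanged. Randomisation balances it in expectation.

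**Conclusion.** The point holds as a mismatch within Table 1. As written, diagnoses of the four conditions between 34 and 40 weeks do not count, although other rows of the table run to 40 weeks. The uncounted period is 6 weeks, or 33% to 49% of the time from birth to 40 weeks, depending on gestational age at birth. How many cases that removes is unknown. For BPD it lies anywhere from none to all under the two assumed assessment ages, and for the other three it cannot be sized.

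The same cut-off applies to both blinded arms, so safety information is lost without bias between arms. The primary outcome is untouched, and death, NEC and late-onset sepsis remain in the harm comparison. Severity is minor: a cheap improvement, not a threat to the trial's conclusions.

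**What to change.** In Table 1, change the time point for BPD, ROP, pulmonary hypertension and hydrocephalus to run until 40 weeks. Take the diagnoses from SNQ and DNQD, and support BPD with the respiratory-support data already collected to 40 weeks. Under Reporting serious adverse events, keep the two-week entry deadline for the interim analyses and add one final update of these four items after 40 weeks.

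The cost is a changed table cell for four rows, one further eCRF update or registry extract, and final safety data for these items that close some weeks later. The interim looks are not delayed. The low cost assumes that the registries or patient records hold these diagnoses up to 40 weeks. The article does not say so for these items, and the sponsor should confirm it. No dose, visit or clinical rule changes.

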### Objectives {7}

The overall aim is to determine whether early probiotic supplementation can be used as a preventative nutritional intervention to reduce the risk of NEC and neonatal mortality among extremely preterm infants born before 28 weeks of gestational age. The effect of supplementation on other common neonatal morbidities will also be studied.

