### Sample size {14}

The sample size calculation is based on the Swedish average incidence of NEC and mortality in extremely preterm infants, which is comparable for Denmark. During the first two to three postnatal days before the intervention is started, the mortality rate is highest among extremely preterm infants. We will calculate the mortality rate from the start of the third postnatal day, as this is the estimated time the enrolled infants will be exposed to the intervention. Based on pooled incidence rate data from SNQ data from the years of 2019, 2020, and 2021, we considered an 18% base rate of the composite outcome NEC and/or mortality, with an estimated 9% overlap. We estimated a 30% reduction, as this was considered clinically relevant and was also the NEC risk reduction rate seen in the ProPrems trial [6]. After analyzing the relative risk for the power analysis, assuming a significance level of 0.05 and 30% reduction rate with interim analysis based on a Pocock boundary at 1/3, 2/3s, and 100% of the information, the proposed enrollment of 1620 patients will have sufficient power [7] to test our hypotheses. Patient enrollment will continue until this number has been reached. Assuming an 80% consent rate, we expect to enroll 1620 infants in 3 years and 8 months.

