#### Primary aim 1 and secondary aims 1–3

In the initial analysis, we will compare baseline characteristics of the study population between allocation groups to ensure that balance was achieved by the randomization. We will report the mean (standard deviation [SD]) or median (first quartile, third quartile) for continuous variables, and count and percentages for categorical variables. The primary analyses will be based on the ITT population including all subjects that were randomized in the study. A crude and a multivariable-adjusted standardized logistic regression will be used to calculate the relative risk (RR) and 95% CI to estimate the effect of probiotic supplementation on the risk of NEC and/or mortality (primary aim) as well as NEC, total mortality, and LOS separately (secondary aims 1–3). The randomization will be stratified per site. Thus, the analysis will adjust for this variable before standardization. A per-protocol analysis accounting for non-compliance will also be performed. All data analyses will be performed using the STATA and R software. A two-sided *p*-value of 0.05 will be considered significant evidence of the effect of the intervention.

#### Secondary aims 4 and 5

The effect of probiotic supplementation on the rate of prescription and duration of antibiotic use during hospital stay (secondary aim 4) and duration of hospital stay (secondary aim 5) will be analyzed using standardized logistic regression and linear regression model.

#### Secondary aim 6

The effect of probiotic supplementation on gut microbiome will be investigated by comparing the alpha and beta diversity of the microbiota samples. Alpha diversity measures the mean diversity within a sample while beta diversity involves a comparison of diversities between samples and will be displayed as a principal coordinate or component analysis plot.

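### Late-diagnosed morbidities are scored plain yes/no in all randomised infants with no provision for death before diagnosis, so any change in mortality modestly biases the safety comparison

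*Protocol article*

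**What the plan says.** In Table 1 (section Outcomes {12}) the serious adverse event block is headed "Necrotizing enterocolitis, death and late-onset sepsis included". The rows beneath it include BPD, pulmonary hypertension, hydrocephalus and ROP. Each has a yes/no metric, is aggregated as a mean or median, and runs to 34 weeks. Respiratory distress syndrome and patent ductus arteriosus are in the same block but are counted from birth. Death also has a row among the primary variables, from the third day to 40 weeks.

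Three statements bear on how these rows are used:

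- Outcomes {12}: "Serious adverse events (SAE) will be collected for interim analysis".
- Interim analyses {21b}: the looks at 540, 1080 and 1620 infants cover safety as well as efficacy and use the method given for the primary aim and secondary aims 1 to 3. The statistical methods section sets that method, standardized logistic regression for a relative risk, in everyone randomised.
- Objectives {7}: "The effect of supplementation on other common neonatal morbidities will also be studied".

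The article gives no survivor denominator, no row combining death with a morbidity, and no rule for an infant who dies first.

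**The concern.** BPD, ROP, hydrocephalus and pulmonary hypertension can be recorded only in an infant who lives long enough to be diagnosed. With a yes/no score and an all-randomised denominator, an infant who dies undiagnosed counts as free of the condition. An infant whose death is prevented can later count as a case. So an arm with fewer deaths tends to show more of these conditions even when the product does nothing to lungs, eyes or brain. An arm with more deaths tends to show fewer.

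The trial is exposed because lower mortality is part of its own hypothesis. The article already combines NEC with death for the primary outcome but does not do so for these rows. At stake is the safety reading, at the committee's looks and in the final report. Apparent protection from a product that raised mortality would be the more troubling error.

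**Working it through.** **The plan's own figure.** Sample size {14} states "we considered an 18% base rate of the composite outcome NEC and/or mortality, with an estimated 9% overlap" and "We estimated a 30% reduction, as this was considered clinically relevant", and relies on "assuming a significance level of 0.05 and 30% reduction rate with interim analysis based on a Pocock boundary". That gives 18% against 12.6%. With 810 per arm and a standard three-look Pocock rule (constant nominal level 0.0221), simulation gives an overall type I error of 0.0497 and power of 80.0%. So "the proposed enrollment of 1620 patients will have sufficient power" reproduces if the unstated power is 80%. The present point does not touch the sample size.

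**Inputs.**

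- Arm size n = 810 (1620 allocated 1:1). The test is two-sided at 0.05, as in the methods section: "A two-sided *p*-value of 0.05 will be considered significant evidence of the effect of the intervention".
- Control mortality m0 is not stated. Reading the 9% overlap as percentage points, risk of NEC + risk of death = 18% + 9% = 27%. Mortality can be no lower than the overlap (9%) and no higher than the composite (18%), so m0 = 9% to 18%.
- Mortality relative risk 0.70 is an assumption. The article plans a 30% reduction for the composite, not for death alone.
- Morbidity among survivors, q, is not stated. 50% is assumed for illustration.
- Morbidity among the extra survivors, qe: first set equal to q, then to 100% as the extreme.
- No true effect of the product on the morbidity.

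**Formulas.** Control rate = q(1 − m0). Active rate = q(1 − m0) + qe × 0.3 × m0. z = difference / √[(p0(1 − p0) + p1(1 − p1))/n]. Chance of a nominal signal towards harm = P(Z > 1.96 − z); with no bias it is 2.5%.

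**Equal risk in the extra survivors (qe = q = 50%).**

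| m0 | Control | Active | Excess | RR | Chance of p<0.05 towards harm |
|---|---|---|---|---|---|
| 9% | 45.5% | 46.85% | 1.35 points | 1.03 | 8% |
| 13.5% | 43.25% | 45.3% | 2.0 points | 1.05 | 13% |
| 18% | 41.0% | 43.7% | 2.7 points | 1.07 | 20% |

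For m0 = 18%: √[(0.41 × 0.59 + 0.437 × 0.563)/810] = 0.0245, z = 0.027/0.0245 = 1.10, and P(Z > 0.86) = 0.195. Under equal risk the RR is (1 − 0.7m0)/(1 − m0), whatever q is. A true relative reduction of about 3% to 6% in morbidity among survivors would therefore be cancelled.

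**Opposite direction.** If mortality instead rose by 30% (an assumption), RR = (1 − 1.3m0)/(1 − m0): 0.883/0.91 = 0.97 at m0 = 9% and 0.766/0.82 = 0.93 at m0 = 18%.

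**What makes it larger.** If every extra survivor has the morbidity, the excess is 0.3 × m0 = 2.7 to 5.4 points. At q = 50% the RR is 1.06 to 1.13 and the chance 19% to 59%. At q = 10% the RR is 1.30 to 1.66 and the chance 43% to 94%.

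**What makes it smaller.**

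- *Windows.* Morbidities are scored to 34 weeks and deaths to 40 weeks. Only deaths before 34 weeks can hide a diagnosis, and the table uses all deaths. If half of the deaths came after 34 weeks, the excess would halve, to about 0.7 to 1.35 points, with a chance of about 5% to 8%.
- *First look.* With 270 per arm and the printed threshold of 0.02205, the chance is about 2% to 5% at q = 50%, against 0.02205/2 = 1.1% with no bias.
- *Lower mortality.* If the 9% overlap is a share of the composite, m0 could be below 9%. At m0 = 5% the excess is 0.75 points and the chance 5%.

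**The composite.** At m0 = 13.5% and q = 50%, death or morbidity is 13.5% + 43.25% = 56.75% in controls and 9.45% + 45.28% = 54.7% in the active arm. If every extra survivor is affected it is 56.75% in both. The false excess disappears in either case.

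**The case against.** The strongest case against is that the article sets no formal between-arm test of BPD or ROP. Methods are assigned to the numbered aims, and these conditions belong to none of them. The sentence in Objectives {7} about other morbidities names neither. Yes/no may be no more than a variable type. There is no harm threshold for these rows, stopping criteria are left to the monitoring committee, and the committee sees deaths by arm in the same block. Denominators in safety tables are often settled in an analysis plan or committee charter, and neither is shown.

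Much of this stands and limits the size of the point. It does not remove it. Table 1 is where the article states its metrics. The serious adverse events are collected for the interim analysis, and the safety looks use an all-randomised method. Read together, these make all randomised infants the denominator for the rates the committee will read, and the bias is in the rates whether or not a test is run.

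A reader might infer something stronger: that a real mortality benefit would show up as excess harm. The documents do not support that. With BPD in 40% to 60% of survivors and in 50% to 90% of infants whose death is prevented, the false excess is 1.3 to 4.9 points and the chance of a nominal signal 8% to 54%. The 54% needs 18% mortality (every composite event a death), 40% BPD in survivors and 90% in the extra survivors. None of these rates is in the article, and the full 30% reduction is applied to death. The article itself reports no significant mortality effect in the larger trial of this product, and 23% lower mortality across pooled trials.

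Nor does the point extend to respiratory distress syndrome or patent ductus arteriosus. They are counted from birth, so cases may precede the intervention.

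**Conclusion.** The point holds in a limited form. For BPD, ROP, hydrocephalus and pulmonary hypertension, the printed metric makes no provision for death before diagnosis, and a change in mortality in either direction would bias the comparison. Under the equal-risk assumptions the bias is a few percent in relative terms and would usually not reach nominal significance, even at full size. It becomes large only if nearly all extra survivors develop the condition, above all where that condition is otherwise uncommon.

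The mortality range, the mortality effect and the morbidity rates are all assumptions. The direction of the bias does not depend on their exact values. The primary analysis and the sample size are unaffected. The correction is worth making because it is cheap and protects the safety reading of a trial intended to inform guidelines.

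**What to change.** In Table 1 and in the monitoring committee's tables, add for each of the four morbidities a row for death or the morbidity, over one common window in all randomised infants. Show it beside the morbidity count and deaths by arm, and state that the morbidity-alone comparison is to be read together with it.

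Do not replace the morbidity-alone row. The composite carries the mortality effect and can hide true organ harm. In the 13.5% mortality example, a true rise in survivors' morbidity from 50% to 52.2% would leave it level: 0.0945 + 0.9055 × 0.522 = 56.7%, against 56.75%. The components must therefore stay visible.

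The cost is a few more rows and some wording. Deaths and these morbidities are already collected. A window ending at 34 weeks needs no new data. A longer one would mean extending the morbidity rows beyond their present limit.
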